### Sample size

Power calculations were based on data from prior published studies [23,24,42,44,57]. These data indicated that the inter-subject variability with respect to impairments, activity, and participation, was moderate to high. Since the outcome measures assess the immediate and long-term effects of rehabilitation in addition to surgery, the calculations were made on the assumption that the changes due to exercise and education will be greater than those expected for education alone. A 50% difference between groups (education, and exercise plus education) is expected based on prior studies, and a 30% subject attrition rate is anticipated. The possible attrition rate is attributed to length of the rehabilitative program, elimination of symptoms, or increase of symptoms and need for a second surgery. All power calculations were based on an alpha level of 0.05 and power of 0.8. Therefore, accounting for attrition, each group would need approximately 50 subjects.

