The study is divided into three phases, a protocol development phase, an implementation or intervention phase, and a follow-up phase. During the protocol development phase, a team of physical therapist researchers and clinicians developed, tested, and standardized the post-surgical intervention and testing protocols. During the intervention phase, a two-group, pretest-posttest design will be used, with participants being randomly assigned to one of two groups: one session of back care education, or a back care education session followed by the 12-week USC Spine Exercise Program. This design will allow for the analysis of the effects of treatment over time. The outcome measures in the study (see below) will be assessed before and after the post-surgical intervention period. The evaluators, as well as the data managers, will be blinded to group allocation. After the end of the intervention phase, follow-up assessments of selected outcome measures will be conducted on all participants every six months, beginning one year and ending five years after the date of surgery (the follow-up phase). The follow-up phase will allow for the analysis of the stability of the effect of treatment over time.

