### Data analysis

The primary and secondary outcome measures will be assessed for immediate and long-term effects using two-factor multivariate analysis of variance (MANOVA), with repeated measures for time. For all multivariate ANOVA tests described, significant main effects will be reported if there are no significant interactions. If significant interactions are found, then one-way ANOVAs will be performed for each main effect. Post-hoc testing will be performed (as necessary) to determine statistically significant pairwise comparisons. Statistical analysis of the results will be performed using the SAS system, version 8.2 (SAS Institute Inc., Cary, NC, USA). All significance levels will be set at p < 0.05.

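### The expected 30% attrition is attributed to recovery, worsening, second surgery and programme length, and a larger sample alone does not protect the comparison from that kind of loss

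*Protocol article*

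**What the plan says.** The Sample size section states that "a 30% subject attrition rate is anticipated" and explains it: "The possible attrition rate is attributed to length of the rehabilitative program, elimination of symptoms, or increase of symptoms and need for a second surgery". It concludes that "accounting for attrition, each group would need approximately 50 subjects". No other response to the expected loss is given.

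Other sections of the article bear on what happens to these participants:

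- **Methods/design:** "follow-up assessments of selected outcome measures will be conducted on all participants every six months", from one to five years after surgery.
- **Outcome measures:** a questionnaire counts as valid only if every section is completed, and an incomplete one is not entered.
- **Follow-up period:** after the one-year visit the questionnaires go by mail, after a telephone call. Participants who report symptoms get the full set (Oswestry, Roland-Morris, SF-36, Subjective Quality of Life, Fear Avoidance, Physical Activity Scale) and the pain scales. Those who report none get only the Physical Activity Scale.
- **Data analysis:** a two-factor MANOVA "with repeated measures for time".
- **Interventions:** three exercise sessions a week for 12 weeks in one arm, after the single education session that both arms receive.
- **Primary and Secondary outcome measures:** second surgery appears in neither list.

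**The concern.** Inflating a sample for dropout works when those who leave resemble those who stay. Here the article itself says they will not. Three of the named causes (symptoms gone, symptoms worse, re-operation) are the results that the trial sets out to measure, and the fourth, programme length, applies to one arm. By the authors' own forecast, the loss is related to outcome and possibly different between arms.

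Two things are at stake. First, the comparison among those who remain may no longer estimate the effect in those randomised, however many are enrolled. Second, the planned power of 0.8 is assured only if loss is unrelated to outcome. In addition, a second operation is a clear treatment failure that the article foresees, yet it is planned only as a reason for loss and not as a result to compare between arms.

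**Working it through.** **Step 1. The plan's own figure.** Inputs from the Sample size section: 50 per group, 30% attrition, alpha 0.05, power 0.8. Evaluable per arm = 50 x (1 - 0.30) = 35, and 35 / 0.70 = 50. The inflation step is consistent, and it counts these participants as absent from the analysis. The 35 itself cannot be reproduced. The effect is given only as "A 50% difference between groups (education, and exercise plus education) is expected based on prior studies", and the variability only as "the inter-subject variability with respect to impairments, activity, and participation, was moderate to high", with no outcome and no SD.

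**Step 2. What 35 per arm can detect.** Two-sided 0.05 is assumed, because sidedness is not stated. Detectable difference = (1.960 + 0.842) x sqrt(2/35) = 0.67 SD by the normal approximation, or 0.68 SD with the t distribution. A 50% difference equals 0.67 SD if the coefficient of variation is about 0.50 / 0.67 = 0.75.

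**Step 3. Where the stated rules lead for each named cause.**

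| Cause of loss | What the article provides |
|---|---|
| Symptoms eliminated | After year 1, only the Physical Activity Scale is sent, so no Oswestry, Roland-Morris, SF-36, Subjective Quality of Life or pain scale data |
| Symptoms worse, second surgery | Counted in expected attrition; second surgery is not an outcome |
| Programme length | Counted in expected attrition; the programme is in the exercise arm only |
| Any missed visit | Repeated-measures MANOVA in its standard form uses only participants with every visit |
| Any incomplete form | Not entered |

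No rule withdraws anyone, but following these rules tends to leave the recovered and the re-operated without primary data.

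**Step 4. Worst-case illustration, loss in both arms.** Assumptions: normal outcome with SD 1, lower is better, true difference 0.68 SD, complete-case comparison, and everyone beyond a cut-off lost. Cut-offs are set on the education arm and applied to both arms.

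| Who is lost | Education lost | Exercise lost | Difference left (original SD) |
|---|---|---|---|
| Best 15% and worst 15% | 30% | 40% | 0.21 |
| Worst 30% | 30% | 11% | 0.40 |
| Best 30% | 30% | 56% | 0.28 |

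For the first row, cut-offs are at -1.036 and +1.036. The retained means are 0 and -0.205, and the retained SD is about 0.546. The standardised difference is 0.205 / 0.546 = 0.376, and with 35 and 30 participants the power is about 0.32.

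**Step 5. A softer version.** If 80% of those below -1.2 SD or above +1 SD leave, the loss is 22% (education) and 28% (exercise), and a true 0.67 SD becomes 0.35 SD.

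**Step 6. The opposite direction.** Take no true effect and let only the exercise arm lose its worst fraction f. The spurious benefit is phi(z) / (1 - f), where phi is the standard normal density and z its 1 - f quantile. For f = 10%, 20% and 30% this gives about 0.19, 0.35 and 0.50 SD.

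**Step 7. A case with no bias.** If 30% leave the exercise arm purely at random, the difference stays at 0.67 SD. With no true effect and the same cut-offs in both arms, no difference appears.

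**The case against.** The strongest reply is that the Sample size section makes a forecast. It says why people may drop out, not that the cured, worsened or re-operated are to be removed, and inflating for expected loss is routine. Methods/design promises follow-up of all participants. A reader might infer that the plan deliberately takes the best and worst results out of the analysis. The article does not support that: it contains no withdrawal or exclusion rule, and absence from the analysis is inferred from the inflation together with the collection and analysis rules. This objection stands and limits the point to expected loss and its likely consequence.

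A reader might also infer that the trial's effect will certainly be biased, or that its power is already lost. The article does not support this either. The illustration puts the whole 30% into sharp outcome tails, gives none to programme length, and takes exercise-arm loss above 30% in two of its three rows. Direction is open, and purely random loss from one arm does no harm.

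It can further be said that analysis populations and missing-data methods belong in the full protocol or analysis plan, which is not shown. That is right, and their absence is not the point made here. The point rests on what the article does state: the causes of loss, sample size as the only remedy, and a mailing rule that stops primary data collection because of the outcome.

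Finally, relabelling alone recovers no data from people who stop attending. This too stands, and it is why the mailing rule has to change as well as the wording.

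**Conclusion.** The point holds in this limited form. The article anticipates loss that depends on outcome and, for programme length, on arm, and its only stated response is to enrol more people. Its own rules on asymptomatic participants, incomplete forms and repeated-measures MANOVA make it likely that recovered or re-operated participants lack primary data, despite the promise to follow everyone.

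The treatment effect may therefore be biased: toward zero if cured or worsened participants leave both arms, in favour of exercise if poor responders leave the exercise arm only. Under worst-case assumed cut-offs, 0.68 SD falls to about 0.2 to 0.4 SD. These figures show how large the problem could become and are not estimates for this trial. They rest on a normal outcome, a complete-case comparison and cut-offs that the article does not give. It should be corrected, because outcome data that were never collected cannot be recovered later.

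**What to change.** - State that participants who stop the programme, become symptom free or have a second surgery remain in follow-up and are analysed in their allocated group.
- List second surgery as an outcome, ask about it at the existing follow-up calls, and report it by arm.
- Change the Follow-up period section so that asymptomatic participants also receive the primary questionnaires and the pain scale forms.
- Reserve the word attrition for withdrawn consent or loss of contact, and reword the Sample size section to match.

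The cost is some additional mailed questionnaires and a little more analysis work. The calls and the mailing schedule already exist, but the primary questionnaires for asymptomatic participants after year 1 are not yet planned, so wording alone is not enough. No treatment changes.

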## Discussion

We have presented the design and rationale for an RCT assessing the immediate and long-term effects of an individualized, multi-factorial exercise program on body functions and structures, activity, participation, and quality-of-life outcome measures in patients who have undergone a single-level lumbar microdiscectomy for the first time. The results of this trial will be presented as soon as they become available.
